### 3.3. Recruitment and Initial Screening

Participants will be recruited through online platforms, including websites, emails, social media, and through flyers on university and hospital campuses. Interested individuals will be contacted by the study coordinator via email to complete an eligibility questionnaire and invited to an online screening visit. During this visit, they will receive comprehensive information about the study’s objectives, tests, and associated benefits and risks. Those who meet the inclusion criteria and are willing to participate will sign the consent form in person before commencing the screening evaluation visit (visit 1).

### 3.4. Baseline Visit

Consenting participants will be enrolled in the trial and undergo baseline clinical assessments, as outlined in Table 1 and Table 2. Following an overnight fast, participants will be screened by collecting medical, dietary, supplementation, and exercise history information and performing the Adult Pre-Exercise Screening System (APSS, 2019, version 2.0) assessment. Baseline evaluations will include the anthropometric measurements; collection of blood, urine, and stool samples; a buccal mucosa swab; an incremental VO_2_peak test on a cycle ergometer; and the completion of a wellbeing and symptoms questionnaire. Research volunteers will also receive instructions from a registered dietitian and study personnel for collecting a 10-day weighed food diary and adhering to fasting protocols. Continuous glucose monitor (CGM) along with a Fitbit device to monitor physical activity and sleep quality and duration will be also set up at baseline assessment.

**Table 1 nutrients-16-04297-t001:** Summary of the visit schedule.

Study Phase	Visit	Visit Title	Approximate Duration of the Visit	Notes
Screening	1	Screening evaluation	3 h	Medical history, blood sample, VO_2_peak test
Phase 1	2	Baseline assessment 1	2 h	Clinical measurements
	3	Start of fasting and cycling exercise/rest period	3.5 h	Fasting starts a night before
	4	End of fasting 1	2 h	Refeeding starts after this visit
	5	End of refeeding 1	2.5 h	4 days after of end of fasting visit
Phase 2	6	Baseline assessment 2	2 h	4 weeks after visit 4
	7	Start of fasting and cycling exercise/rest period	3.5 h	Fasting starts a night before
	8	End of fasting 2	2 h	Refeeding starts after this visit
	9	End of refeeding 2	2.5 h	4 days after of end of fasting visit
	10	Follow up assessment	4 h	4 weeks after visit 8

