In recent years, periodic prolonged fasting has gained renewed attention due to claims that it promotes longevity and improves health by influencing cellular ageing and reducing disease risk factors. However, despite its growing popularity, the precise molecular and cellular adaptations and potential risks associated with fasting in humans remain poorly understood [8,9]. For example, one of the key mechanisms linked to fasting’s benefits is autophagy, a tightly regulated process responsible for degrading and recycling damaged organelles and misfolded proteins, thus maintaining cellular homeostasis with ageing [10]. While evidence from animal models supports fasting-induced autophagy, human studies have largely relied on indirect and imprecise markers, such as protein or mRNA levels, as indicators of autophagic activity [11]. The precise dynamics of autophagic flux—the rate at which autophagosomes sequester and degrade cellular components—remain largely underexplored in humans during prolonged fasting. A key barrier to understanding human autophagy has been the reliance on cell culture methods that disrupt the natural nutritional and endocrine signalling present in blood. By maintaining cells in whole blood, which is physiologically intact during flux measurement, we aim to capture how autophagic flux responds to interventions like fasting while preserving the genetic, nutritional, and hormonal factors unique to each individual [12].

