### 3.2. Eligibility Criteria

Participants must meet the following criteria: (1) healthy males and females without disabilities that may hinder cycling exercise participation; (2) aged between 18 and 70 years old; (3) with a BMI within the range of 20–40 kg/m^2^; (4) able to adhere to all study assessments and procedures, including exercise and fasting interventions. Participants will be excluded based on the following conditions: (1) pregnant, breastfeeding, or of childbearing potential and unwilling to implement contraception during the study; (2) a history of chronic diseases that could impede exercise tests or compromise result interpretation; (3) the presence of comorbidities including hypertension, diabetes mellitus, or known cardiovascular disease; (4) a history of supplement or medication use that may affect result interpretation; (5) health conditions, dietary requirements, or psychosocial factors that may interfere with study participation and compliance; (6) unintentional weight loss exceeding 10% of body weight in the past 5 years, as well as smoking, psychiatric, or behavioural issues (e.g., a history of drug/alcohol abuse or eating disorders); and (7) the inability to perform cycling exercises, evidenced by an inability to complete the incremental peak power test during the baseline assessment or the 90 min glycogen-depleting exercise at the beginning of the fasting intervention (Table 3).

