## 4. Fasting and Exercise Interventions

### 4.1. Three-Day Fasting Protocol

Participants will undergo a three-day (approximately 84 h, including 12 h overnight fasting before clinic visit) water-only fast at home, with remote monitoring and support from the study team. Throughout the fasting and refeeding phases, participants will report their wellbeing and symptoms via an online questionnaire and can contact study coordinators through email, SMS, or phone. Adherence will be monitored using a continuous glucose monitor (CGM) and by measuring morning and evening beta-hydroxybutyrate (BHB) ketone and glucose levels through fingerpick capillary blood. Participants will communicate their glucose and ketones readings to the trial coordinator, who will also review the data stored in the device during clinic visits. The CGM data will be streamed to an online dashboard monitored by research staff.

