A week prior to the fasting intervention, participants will transition to consuming only water for hydration to reduce dependence on caffeine and caloric beverages. They will refrain from strenuous exercise for 48 h before the fasting assessment. On the day before fasting begins, participants will consume only water from 9 PM onward and record all food and drink intake in a diary for submission after the refeeding assessments. During fasting, participants are advised to drink 2–3 litres of water daily, with unflavoured carbonated and mineral water permitted. If participants find it too challenging to continue water-only fasting, they will be provided with 250 mL of vegetable broth sourced from Undivided Food Co., Sydney, Australia, which contains 110 kJ of energy, 0.8 g of protein, 0 g of fat, 5.8 g of carbohydrate and 375 mg of sodium per 250 mL serving. A maximum of two servings per day will be provided. Light physical activities such as walking, yoga, or stretching are encouraged, while strenuous exercise is not recommended. On the last fasting day, following clinic assessments, food will be gradually reintroduced, starting with vegetable broth and transitioning to a low-carbohydrate vegetarian diet. This initial diet will consist of small portions of non-starchy vegetables, salads, and soups for the first day, then gradually transitioning to their normal diet by the end of the refeeding period. This gradual reintroduction of food aims to minimise potential adverse effects and gastrointestinal symptoms. The vegetable broth will be offered upon completion of the fasting visit, along with instructions for the subsequent four days of the refeeding period. The rest of the meals of the refeeding period will not be provided; however, the participants will log all the food and drink into the food diary. Once the refeeding period concludes, participants will be instructed to resume their usual lifestyle for a 4-week washout period.

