### 5.2. Secondary Outcomes

Secondary outcomes to be assessed include:Body weight, waist circumference, and body composition measured by DXA and Bod Pod;Autonomic function, including heart age and heart rate variability, assessed through resting electrocardiography;Blood pressure;Endothelial function evaluated by flow-mediated vasodilation;Continuous monitoring of blood glucose kinetics;Capillary ketones and glucose levels using a portable test strip-based meter;Oral glucose tolerance test to assess glucose tolerance and insulin action;Serum fasting free fatty acids, BHB, acetoacetate, BHB-to-acetoacetate ratio, and lipid profile;Serum concentration of insulin, IGF-1, IGFBP-1, IGFBP-2, IGFBP-3, FGF21, cortisol, testosterone, estradiol, sex hormone-binding globulin (SHGB), T3, Klotho, BDNF, and Beta-Amyloids (Aβ40 and Aβ42);Markers of inflammation, including high-sensitivity C-reactive protein, cytokines (IL-6, TNF-alpha), and chemokines (MCP1);Markers of oxidative stress, including urinary F-2 isoprostanes and 8-hydroxy-2′-deoxy Guanosine.

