### 5.6. Statistical Analysis Plan

Statistical analysis will employ ANOVA with a repeated measures design and/or linear mixed model regression. The models will include baseline characteristics such as age, sex, prior fasting experience, and habitual dietary patterns as covariates. While our sample size is primarily powered for detecting changes in the primary outcome, we will conduct exploratory analyses of these potential modifying factors, acknowledging that subgroup analyses will be hypothesis-generating rather than definitive. Linear regression and/or general additive models will analyse the relationship between habitual dietary intake and baseline measures, as well as the magnitude of response to fasting. Additionally, correlation analyses will be conducted to evaluate the relationship between autophagic flux readouts and quantified molecular markers, aiming to identify potential biomarker candidates for future studies. Given the sample size, analyses stratified by factors such as sex, age groups, or physical activity levels will be considered exploratory and interpreted with appropriate caution.

Exploratory multi-omics outcomes will be integrated via a multi-step approach. First, each omics layer (e.g., metabolomics, proteomics, or transcriptomics) will be analysed independently using standard workflows. Integration will then proceed through: (1) correlation network analysis to identify associations between molecules across omics layers; (2) pathway enrichment analysis to uncover biological processes affected across these layers; and (3) machine learning approaches, including sparse partial least squares discriminant analysis (sPLS-DA), to identify key molecular signatures associated with changes in autophagic flux. Specifically, metabolomics data will identify altered metabolic pathways, which will be cross-referenced with proteomic changes in related enzymes and regulatory proteins. Additionally, changes in the gut microbiome will be correlated with plasma metabolites to identify potential microbe-derived metabolites. This integrated analysis aims to provide a systems-level understanding of fasting-induced molecular changes and their relationship to autophagic flux. Established multi-omics integration tools such as mixOmics and MOFA+ (Multi-Omics Factor Analysis) will be employed for the analysis.

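### Phase 2 is timed by calendar only, so in naturally cycling participants the two fasts may, and for many would, fall at different menstrual-cycle phases, which adds avoidable noise to the B-minus-A contrast for estradiol and other sex hormones

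*Protocol article*

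**What the plan says.** - **Timing of Phase 2.** Table 1 (section 3.4) puts visit 6 "4 weeks after visit 4". Visit 4 is the end of the first fast. Visit 7, the start of the second fast, follows visit 6 after an interval that is not stated.
- **Washout in the text.** Section 4.1 counts from a different point: "Once the refeeding period concludes, participants will be instructed to resume their usual lifestyle for a 4-week washout period". Table 1 puts the end of refeeding (visit 5) 4 days after visit 4.
- **Length of each fast.** Section 4.1 describes a "three-day (approximately 84 h, including 12 h overnight fasting before clinic visit) water-only fast at home". That leaves 84 − 12 = 72 h, or 3 days, from visit 3 to visit 4.
- **Lead-in.** Section 4.1 states: "A week prior to the fasting intervention, participants will transition to consuming only water for hydration". It does not say whether that week begins at the baseline visit.
- **Who can enrol.** Both sexes are eligible from age 18 to 70. Section 3.2 excludes those who are "pregnant, breastfeeding, or of childbearing potential and unwilling to implement contraception during the study". No type of contraception is named, so a woman using a non-hormonal method, and therefore cycling naturally, can take part.
- **Outcomes.** The secondary outcomes in section 5.2 include "cortisol, testosterone, estradiol, sex hormone-binding globulin (SHGB".
- **Model.** Section 5.6 states: "The models will include baseline characteristics such as age, sex, prior fasting experience, and habitual dietary patterns as covariates".
- **Schedule of procedures.** Table 2 has no entry for cycle day.

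**The concern.** The crossover earns its small sample through the within-person comparison. That comparison is sharp only when conditions that vary within a person are similar in the two periods, or are recorded so that they can be adjusted for. Cycle phase is one such condition for sex hormones. A fixed calendar interval does not hold it constant, and no scheduled item records it.

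The four covariates given as examples in section 5.6 describe the person and not the period. They take the same value under both interventions, so they cancel from the B-minus-A contrast and cannot absorb a difference in phase.

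At stake is the precision of the estradiol comparison, and of other sex-hormone outcomes so far as they follow the cycle. Cycle day that is not asked for at the visits is hard to reconstruct afterwards.

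**Working it through.** **Interval between the fasts.** Take visit 3 as day 0. Visit 4 is day 3, visit 6 is day 3 + 28 = 31, and visit 7 is day 31 + g. On an assumed 28-day cycle the offset is 31 + g − 28 = 3 + g days.

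| g (days) | Fast to fast (days) | Offset (days) |
|---|---|---|
| 0 | 31 | 3 |
| 3 | 34 | 6 |
| 7 | 38 | 10 |
| 10 | 41 | 13 |

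The article does not give g. A value of 7 would follow if the water-only-drinks week started at the baseline visit. About 3 would follow if the 10-day food diary ran from the baseline visit to the end of refeeding (10 − 3 − 4 = 3). Both are inferences. If the 4 weeks run from visit 5, as section 4.1 has it, 4 days are added: 35 days at g = 0, an offset of 7.

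**Dependence on cycle length.** At g = 0 (31 days) the offset is 7 days for a 24-day cycle and 1 day for a 30-day cycle. With cycle length assumed normal, mean 28.5 and SD 3 days, the share of women whose second fast starts within 3 days of the same phase is 53% at g = 0, 20% at g = 3, and 2% at g = 7 or 10.

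**Added variance.** Model the cycle as a sinusoid of amplitude a with a random starting phase. For an offset of d days, the cycle variance of B − A is a²(1 − cos(2πd/28)). With residual SD s in each period, the variance of B − A is 2s² + a²(1 − cos(2πd/28)).

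**Estradiol.** The article gives none of the following, so all are assumptions: 10 naturally cycling completers; a peak-to-trough range of 3-fold with s = 0.25, or 5-fold with s = 0.35, on the log scale. Then a = ln(3)/2 = 0.549 (a² = 0.302) or a = ln(5)/2 = 0.805 (a² = 0.648). The 95% limits for the B/A ratio lie a factor exp(t × SD/√10) either side, with t(0.975, 9 df) = 2.262.

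| Offset (days) | 1 − cos | Variance, 3-fold | Factor | Variance, 5-fold | Factor |
|---|---|---|---|---|---|
| 2 (aligned) | 0.099 | 0.125 + 0.030 = 0.155 | 1.33 | 0.245 + 0.064 = 0.309 | 1.49 |
| 3 | 0.218 | 0.125 + 0.066 = 0.191 | 1.37 | 0.245 + 0.141 = 0.386 | 1.56 |
| 6 | 0.778 | 0.125 + 0.235 = 0.360 | 1.54 | 0.245 + 0.504 = 0.749 | 1.86 |
| 10 | 1.623 | 0.125 + 0.490 = 0.615 | 1.75 | 0.245 + 1.051 = 1.296 | 2.26 |

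**Change from the pre-fast value.** Over the 3 days of a fast the cycle itself moves. The change score keeps an amplitude of 2 sin(3π/28) × a = 0.66a, and 0.66² = 0.44. Differencing therefore removes about 56% of the cycle variance and leaves 44%. If residuals are independent, it also doubles the residual part to 4s². At a 10-day offset the 3-fold case is then 0.250 + 0.44 × 0.490 = 0.464, a factor of 1.63, against 0.250 + 0.44 × 0.030 = 0.263, a factor of 1.44, if aligned within 2 days. The gap narrows but does not close.

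**The case against.** **Four weeks is about one cycle, so the schedule aligns itself.** It would if the 4 weeks ran from fast to fast. They run from the end of the first fast to the second baseline visit, so the fasts start at least 31 days apart. What stands is that g is unstated and cycle length varies. With a very short gap about half of cycling women would be close to aligned. Misalignment is likely for many but not certain for all.

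**This belongs in the case report form or the SAP.** In part it does. Table 2 takes a medical history at visits 1 and 6, where the question could be asked, and the covariate list opens with "such as", so it is not closed. But the calendar interval is a stated rule, a history at visit 6 does not date both fasts, and an SAP cannot adjust for a cycle day that was not collected.

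**A reader might infer a loss on the primary outcome.** The introduction says that the whole-blood assay works while "preserving the genetic, nutritional, and hormonal factors unique to each individual", which may seem to tie flux to the cycle. That sentence contrasts whole blood with cell culture and says nothing of menstrual variation, and the article gives no cycle amplitude for flux. Any loss is therefore hypothetical and sensitive to the assumptions. Suppose a cycle amplitude of 0.5 to 1.0 residual SD, a 10-day offset, and 25% to 50% of 20 completers cycling. The variance of B − A in those women would be 1.19 to 1.73 times the aligned value, equivalent to 20/(1 + 0.25 × 0.19) = 19.1 down to 20/(1 + 0.5 × 0.73) = 14.7 completers. Section 5.5 sizes the trial on a change, and on that scale the ratio falls to 1.04-1.16, or about 19.8 to 18.5 completers. At an amplitude of 0.25 the loss is negligible even without differencing (19.8 to 19.5).

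**A reader might also infer bias.** Starting phase is arbitrary and the sequence is randomised, so the contrast stays unbiased in expectation.

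**Estradiol is one analyte in a long list, with no power claim of its own.** That is true, and it limits the weight of the point.

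**Conclusion.** The point holds as one of precision for the sex-hormone outcomes. The calendar rule puts the fasts 31 + g days apart, naturally cycling women can enrol, estradiol is a named secondary outcome, and nothing in the schedule or the named covariates accounts for phase.

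Under the stated assumptions the confidence factor for the B/A estradiol ratio goes from 1.33-1.49 when aligned to 1.37-1.56 at a 3-day offset, 1.54-1.86 at 6 days and 1.75-2.26 at 10 days. At the short end the cost is slight. At 10 days only a large effect on estradiol could be told from none in these women. The size rests on the unstated gap g, a sinusoidal 28-day cycle, and assumed figures for the estradiol range, the residual SD and the number of cycling completers.

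The documents support neither a claim of bias nor a stated loss of power for autophagic flux.

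**What to change.** 1. Record cycle day and hormonal contraceptive use at visits 3/4 and 7/8.
2. Enter cycle phase as a period-level covariate in the analyses of estradiol and the other sex hormones. For flux and flow-mediated dilation, use it in a sensitivity analysis only.
3. Optionally, where feasible and without shortening the washout, word visit 6 as at least 4 weeks after visit 4, so that visit 7 can be booked near the same cycle day as visit 3.
4. Reconcile the two starting points for the 4 weeks: visit 4 in Table 1 and the end of refeeding in section 4.1. State the gap from visit 6 to visit 7.

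**Cost.** Items 1 and 2 need one extra question at visits already held and add no time to the schedule. A phase term fitted in few women will be imprecise. Item 3 is a real trade-off. Waiting for the same day of a 28-day cycle delays Phase 2 by 28 minus the offset, which is 25 days at g = 0 and 18 days at g = 7. The delay falls on cycling participants only, gives them a longer washout than the others, and prolongs follow-up in a trial that already allows for 20% dropout. Irregular cycles cannot be booked this way and can only be adjusted for.

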### 3.5. Randomisation

Participants will be randomly assigned using a web-based system in REDCap, employing random permuted blocks with a block size of four. Randomisation will occur at the beginning of visit 3, after all baseline measurements have been completed (Figure 1, Table 1). The study coordinator will disclose group assignments to both the study team and the participant upon their arrival for the clinic visit #3. While blinding participants and investigators is not feasible due to the nature of the intervention, those conducting sample analysis and statistical analysis will remain blinded to group allocations, when possible.

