## 3. Methods

### 3.1. Study Design

The PROFASTA trial is a randomised, single-centre, two-period, two-sequence crossover study, involving a total sample of 25 participants. Participants will be randomly assigned into two groups, with each group undergoing two different interventions in separate phases (Figure 1). By the study’s end, all participants will have completed both Intervention A and Intervention B, ensuring robust within-subject comparisons to strengthen the validity of the findings. Intervention A consists of a three-day water-only fast, while Intervention B includes a three-day water-only fast that is preceded by a single session of glycogen-depleting endurance exercise conducted on the first day of the fasting period, following an overnight fast. Detailed clinical visits and procedures are outlined in Table 1 and Table 2. This study has been approved by the Sydney Local Health District Ethics Committee (2022/ETH00617), and all study visits will take place at the Charles Perkins Centre-Royal Prince Alfred Hospital (CPC-RPA) clinic. The protocol has been prepared using the SPIRIT reporting guidelines [26].

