### 4.2. Exercise-Induced Glycogen Depletion (80–90 Min)

The exercise protocol, adapted from seminal glycogen depletion studies [27,28], will take place after participants arrive for the start of the fasting visit following an overnight fast and after all initial assessments are complete. Power outputs for the cycle ergometer will be determined based on the incremental VO_2_peak test performed during the screening visit. Participants will engage in 60 min of cycling at a constant power output corresponding to 60–70% of their peak VO_2_, maintaining a cadence of 60–70 rpm, which is classified as moderate-intensity physical activity. After a 5 min rest, the participants will perform repeated 1 min sprints at 90 rpm and 90–100% of their VO_2_peak equivalent power output, with 1 min rest intervals between sprints. The exercise session will conclude after ten sprints or if participants cannot maintain a pedalling rate of ≥80–90 rpm for 1 min. Verbal encouragement will be provided throughout the session, during which heart rates will be recorded using Polar H10 chest strap heart rate monitors. Throughout the exercise session, participants’ fatigue levels will be monitored using the Rating of Perceived Exertion (6–20 RPE) scale, with heart rate and RPE recorded every 10 min during steady-state cycling and after each sprint. The exercise will be terminated if participants report severe fatigue (RPE ≥ 19), experience any adverse symptoms (dizziness, nausea, unusual shortness of breath), or if heart rate exceeds 95% of age-predicted maximum for more than 3 min. If a participant cannot complete the full protocol, a minimum of 60 min of steady-state cycling plus three sprints will be considered sufficient for partial glycogen depletion, allowing continued participation in the study. Those unable to meet these minimum requirements will be withdrawn from this arm of the trial.

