### 5.4. Safety Monotoring and Reporting

Participant safety is prioritised through comprehensive screening, monitoring, and risk mitigation strategies. Screening excludes individuals with conditions that could increase risk, including a history of hypoglycemic episodes, cardiovascular problems, or eating disorders. During the fasting period, participants are monitored via continuous glucose monitoring, additional twice-daily glucose and ketone measurements, and regular check-ins with study staff. Medical supervision is provided during exercise sessions, with clear stopping criteria based on heart rate, blood pressure, and symptoms. Emergency protocols include immediate exercise termination criteria and breaking-fast procedures if participants experience severe adverse effects. Adverse events (AE) and serious adverse events (SAE) will be systematically documented and reported throughout the study to prioritise participant safety. Each event will include details such as a description, onset date, end date, severity, assessment of relatedness to the trial intervention or device, and any actions taken in response. Research investigators will use their clinical expertise to determine whether an AE necessitates the participant’s removal from the study. SAEs will be reported to the primary investigator within 24 h of the study team’s awareness. The complete course of the SAE, including any administered therapy, will be communicated to the study sponsor. Additionally, any significant safety concerns will be reported to the local Human Research Ethics Committee and Research Governance Officers.

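### The reason given for not blinding investigators does not cover those who acquire or read FMD, resting ECG and manual measurements at the post-fast visits

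*Protocol article*

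**What the plan says.** Section 3.5 (Randomisation) makes three statements about blinding.

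- It rules blinding out for two groups together: "blinding participants and investigators is not feasible due to the nature of the intervention".
- It sets who learns the allocation, and when: "The study coordinator will disclose group assignments to both the study team and the participant upon their arrival for the clinic visit #3".
- It keeps blinding for one remaining group: "those conducting sample analysis and statistical analysis will remain blinded to group allocations, when possible".

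Section 3.1 defines what separates the arms. Both include the three-day water-only fast, and Intervention B adds "a single session of glycogen-depleting endurance exercise conducted on the first day of the fasting period". Section 4.2 places that session within the start-of-fasting visit, "after all initial assessments are complete".

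Section 5.2 lists "Endothelial function evaluated by flow-mediated vasodilation" among the secondary outcomes, together with autonomic function from resting ECG, blood pressure and waist circumference. Neither section 3.5 nor section 5.2 names a blinded assessor for any of these.

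**The concern.** Section 3.5 treats investigators as one group and gives one reason for all of them. The exercise session is visible to the participant and to whoever supervises it. An operator or reader who sees the participant, or only a stored recording, days later is in a different position. The stated reason does not explain why that person must know the arm.

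The outcomes at stake are those in which a person's judgement can enter. FMD acquisition and reading is the clearest case, tape-measured waist is another, and ECG processing may be a third. The team also has a directional hypothesis: sections 2 and 6 expect exercise to enhance the response to fasting. A reader who knows the arm and shares that expectation could shift readings in one direction for B relative to A, without intending to.

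The crossover gives no protection. Each participant serves as their own control, which removes stable differences between people. A reading shift tied to the intervention goes directly into the within-person B minus A contrast. With only two sequences, the phase 1 arm also reveals the phase 2 arm, so a single disclosure at visit 3 covers both periods.

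**Working it through.** The main check compares sections of the protocol article. The plan has no figure of its own on this point to reproduce.

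**1. Where the arms differ.** By sections 3.1, 3.7 and 4.2, the difference is one exercise session at visit 3 or visit 7. Table 2 ticks the exercise row at visits 1, 3 and 7 only, and visit 1 is the screening test that everyone performs.

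**2. How far the post-fast visits are from that session.** Section 4.1 gives a fast of about 84 h, of which 12 h precede the start-of-fasting visit. Visits 4 and 8 therefore fall about 84 − 12 = 72 h after that visit. Table 1 puts visits 5 and 9 four days later, so about seven days after it.

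**3. What is measured there.** Table 2 gives one schedule for both arms. FMD, the resting ECG and the physical examination (blood pressure, weight, waist and hip) are all ticked at visits 4, 5, 8 and 9.

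**4. Who is shielded.** Section 3.5 keeps blinding for sample analysis and statistical analysis. In its natural sense, sample analysis means laboratory work. That covers the primary outcome, a flux assay in PBMCs, and most biomarkers in sections 5.2 and 5.3. It does not clearly cover acquiring or reading FMD or ECG, or measuring a waist.

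**5. Timing at visit 3.** Disclosure takes place on arrival. Exercise follows that visit's initial assessments, and Table 2 ticks FMD at visit 3. If FMD is one of those initial assessments, even this pre-exercise reading is taken with the allocation known.

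**6. Illustration of sensitivity.** The number of completers follows from section 5.5: 25 recruited with 20% dropout gives 25 × 0.8 = 20. The other inputs are assumptions that the documents do not contain: no true A-versus-B difference in FMD, a paired SD *s* of the B minus A difference of 2 to 3 percentage points, and an arm-linked reading shift *b* of 0.5 or 1.0 point.

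For a two-sided 5% paired t test with n = 20 (19 degrees of freedom, critical value 2.093), the rejection probability is that of a noncentral t with noncentrality δ = b√n / s:

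| Shift b | SD s | δ = b√20 / s | Rejection probability |
|---|---|---|---|
| 0.5 | 2.0 | 1.118 | 18.6% |
| 0.5 | 2.5 | 0.894 | 13.6% |
| 0.5 | 3.0 | 0.745 | 10.9% |
| 1.0 | 2.0 | 2.236 | 56.45% |
| 1.0 | 2.5 | 1.789 | 39.7% |
| 1.0 | 3.0 | 1.491 | 29.4% |

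In whole per cents, the nominal 5% becomes 11–19% for a 0.5-point shift and 29–56% for a 1.0-point shift.

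**The case against.** The strongest case on the other side has four parts.

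**The arms may be distinguishable after the fast.** A reader might infer from the common schedule that the arms look the same at every post-fast visit and that assessors are unblinded without need. The documents do not say so. Section 6 lists fatigue and muscle soreness as exercise-related risks. Participants know their arm, and at those visits they complete a symptoms questionnaire and an adverse-event assessment. Blinding of staff in the room would be imperfect. This stands, but it does not affect a coded recording read offline.

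**Most of the trial is already protected.** A reader might infer that the primary comparison is compromised. It is not, as far as the text shows: the primary outcome is a laboratory assay within the group that stays blinded when possible. This stands and limits the point to clinic-measured secondary outcomes.

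**Adverse-event ratings are a poor example.** Section 5.4 records "severity, assessment of relatedness to the trial intervention or device" for each event. One might extend the criticism to these ratings. But Intervention B includes the exercise, so relatedness to the intervention cannot be judged without knowing whether exercise took place, and events at visits 3 and 7 can arise during visible, supervised exercise. Relatedness therefore forms no part of this point. At most, severity at post-fast visits could be graded before the arm is consulted.

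**The article is condensed.** It does not say who reads FMD or ECG recordings, or whether this happens offline, and such details often sit in a fuller protocol. Blood pressure and heart rate variability may also come largely from devices. This is fair as regards the details. However, section 3.5 is not merely silent: it declares investigator blinding infeasible, orders disclosure to the study team and lists who remains blinded. That rule and its reason can be judged as written.

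**Conclusion.** The point holds for a limited set of outcomes. The reason in section 3.5 justifies unblinded participants and unblinded staff at visits 3 and 7. It does not justify unblinded acquisition or reading of FMD, resting ECG and manual measurements at visits 4, 5, 8 and 9. As written, these secondary outcomes are exposed to arm-linked reading bias that the crossover leaves in the contrast.

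The size of any such bias is unknown. A reader might take the error rates above as a forecast. They are not: they show how sensitive a 20-person paired comparison would be if a shift of that size occurred consistently in one direction, and both the shift and the SD are assumed. No sample size, power figure or primary analysis in the plan changes. This is an inexpensive improvement worth making, not a flaw in the main comparison.

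**What to change.** Revise section 3.5 as follows.

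1. Limit disclosure of the allocation to the coordinator, the participant, the staff supervising visits 3 and 7, and those managing safety.
2. Store FMD and ECG recordings under random codes that hide intervention and period, and have the existing readers read them offline after coding.
3. Where the rota allows, do not tell measuring staff at visits 4, 5, 8 and 9 the arm, and ask participants not to mention it.
4. Optionally, grade adverse-event severity at post-fast visits before the arm is consulted. Leave relatedness assessment as it is.

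The cost is new wording, file coding and a rota constraint, with no extra visit, procedure or reader. Two limits remain. Participants or their symptoms will sometimes reveal the arm. If the person who acquired a recording also reads it, coding protects less well; the documents give no staffing information to settle how often that would happen.
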